### Interim analyses {21b}

There are no anticipated problems that are detrimental to the participants.

### Methods for additional analyses (e.g., subgroup analyses) {20b}

Analyses for primary and secondary outcomes will include (i) subgroup evaluation through post hoc analysis and (ii) adjustment for potential confounders, so no further additional analyses will be performed.

### Methods in analysis to handle protocol non-adherence and any statistical methods to handle missing data {20c}

An evaluation of the type of missing data will be performed to detect any missing not-at-random outcome data. In the case of missing not-at random or missing outcomes of main interest, a subsequent data-imputation technique (Bayesian imputation performed in the context of structural equation modeling) will be applied to obtain complete outcome data.

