### Sample size {14}

The primary outcome measures will be represented by changes in impulsive behaviors (established by the Checklist for Impulsive Behaviors) and by changes in emotional regulation skills (determined by the DBT-Ways of Coping Checklist).

Precisely, the outcome will be evaluated in terms of change (pre/post) in percentage of “yes” answers in the two groups (treated and control), where “yes” is defined as a difference of at least one category toward improvement from baseline. More specifically, the scores of the Checklist for Impulsive Behaviors are measured on a Likert scale. Therefore, a “yes” answer implies a decrease in the frequency of impulsive behavior; for example, from the category “two or three times a week” to the category “one time a week.” In a similar manner, a “yes” answer for the DBT-Ways of Coping Checklist means a decrease in the use of dysfunctional skills; for example, from the category “regularly used” to “sometimes used,” or vice versa for functional skills.

We assumed that at baseline, there would be a between-group difference by chance of 7% (i.e., 1/15 yes answers, where 15 is the total number of checklist items) on the Checklist for Impulsive Behaviors and that this difference would increase by up to 13% (i.e., 2/15 yes answers) after the intervention. Based on these assumptions and applying a two-sided test for paired binomial proportions, with a significance level equal to 0.05 and a power of 0.8, the estimated sample size was *n* = 340 (170 per group). Moreover, considering a drop-out rate of 20%, the minimum sample size (MSS) reached *n* = 426 (213 per group).

In the same way, we assumed that on the DBT-Ways of Coping Checklist, there would be a difference by chance of 7% (i.e., 4/59 yes answers, where 59 is the total number of the checklist DBT items) at baseline, and that this difference would increase by up to 20% (i.e., 12/59 yes answers) after the intervention. This last hypothesis was made considering that, given the focus of treatment, we expected a greater change in emotional regulation skills than in dysfunctional behaviors. Based on these considerations and applying a two-sided test for paired binomial proportions, with a significance level equal to 0.05 and a power of 0.8, we reached an estimated sample size of *n* = 84 (42 per group).

In sum, due to both the outcome measures and related sample size estimations, the final sample size needed was 426 students.

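### The plan sets out to detect missing-not-at-random outcomes, which observed data cannot show, and states no missing-not-at-random remedy for outcome-related dropout

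*Protocol article*

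**What the plan says.** The missing-data rule is in the Protocol article, section {20c} (non-adherence and missing data). Its first step is diagnostic: "An evaluation of the type of missing data will be performed to detect any missing not-at-random outcome data".

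The second step gives two alternative triggers for imputation: "In the case of missing not-at random or missing outcomes of main interest, a subsequent data-imputation technique". The technique is "Bayesian imputation performed in the context of structural equation modeling", and it "will be applied to obtain complete outcome data". The section names no missingness model, shift parameter or pattern-mixture term, and it does not say what the imputation assumes about the missing values.

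Four other sections bear on the point:

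- Section {20a} plans generalized mixed models over time and between groups for the behaviours and skills that form the primary outcomes.
- Section {20b} lists post hoc subgroup evaluation and confounder adjustment, and ends "so no further additional analyses will be performed".
- Section {14} inflates the sample size for loss: "considering a drop-out rate of 20%, the minimum sample size (MSS) reached" 426, or 213 per group.
- Section {17a} states that participants are not blinded and that outcomes are self-reported.

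**The concern.** Missing at random and missing not at random differ only in how missingness depends on values that nobody recorded. Collected data can show that dropouts differ from completers on measured characteristics, which is evidence against missing completely at random. They cannot show whether dropouts also differ on the unseen outcome once those characteristics are allowed for. The diagnostic therefore promises an answer that it cannot give.

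The response does not match the diagnosis either. Unless a departure is modelled explicitly, imputation from a structural equation model predicts missing values from observed relationships, which is to assume missing at random. A declared missing-not-at-random pattern would be answered by a method resting on the opposite assumption.

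Selective non-response is plausible here. Students know their allocation, report their own outcomes, and are asked in the impulsive-behaviour checklist about self-injury and substance use. If those who benefit least are more likely to miss the post-intervention assessment, the estimate is biased, while the plan reads as though that possibility had been checked and handled.

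**Working it through.** **1. The plan's own figure.** From section {14}: 170 per group before loss, 20% dropout. 170 / (1 − 0.20) = 212.5, rounded up to 213 per group and 426 in total. This matches the plan. The anticipated missing number is 213 − 170 = 43 per arm.

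**2. Can the diagnostic work?** Take one arm of 213 with 170 observed, of whom 22 are classed as improved (22/170 = 12.9%, an assumed figure). Let q be the unknown proportion improved among the 43 missing. The full-arm proportion is (22 + 43q) / 213.

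| q among the missing | Observed data | Full-arm proportion |
|---|---|---|
| 0% | 22 of 170 | 22.0/213 = 10.3% |
| 13% | 22 of 170 | 27.6/213 = 13.0% |
| 30% | 22 of 170 | 34.9/213 = 16.4% |

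The middle column never changes. No evaluation of the observed data can tell these three situations apart.

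**3. What does missing-at-random imputation do under each mechanism?** This was simulated with assumed inputs: true effect 0.30 SD, baseline-to-outcome correlation 0.5, about 20% missing. Intervention-arm dropout depended either on baseline (missing at random) or on the post-intervention score itself (missing not at random). Control dropout was purely random. Missing values were predicted from baseline within arm.

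| Dropout mechanism | Complete cases | Missing-at-random imputation | Truth |
|---|---|---|---|
| At random | 0.389 | 0.300 | 0.300 |
| Not at random | 0.477 | 0.437 | 0.300 |

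Imputation removes the bias in the first row. In the second row it leaves 0.137 of a complete-case bias of 0.177, about three quarters.

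**4. Size on the proportion-improved scale.** Let m be the fraction missing in each arm. Let k_E and k_C be the shortfalls in proportion improved among missing students, relative to observed students in the intervention and control arms. If the imputation gives missing students the rate of observed students in their arm, then

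overstatement of the arm difference = m × (k_E − k_C).

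With m = 0.20:

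| k_E (points) | k_C (points) | Overstatement (points) |
|---|---|---|
| 5 | 0 | 1.0 |
| 10 | 0 | 2.0 |
| 13 | 0 | 2.6 |
| 13 | 7 | 2.6 − 1.4 = 1.2 |
| 0 | 7 | −1.4 |

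The shortfalls are assumptions; the documents give none. The last row shows that the bias can also hide part of an effect.

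**5. What the two triggers do.** Outcomes of main interest are most naturally read as the primary outcomes. If these are missing, the second trigger applies whatever the diagnostic says, and the same imputation follows. The diagnostic can change the handling only of other outcomes, and there it turns on a distinction that the data cannot make.

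**The case against.** The best defence is that this is a journal article, that an analysis plan may exist, and that the content of an imputation model, its pooling and any range of shifts commonly belong there. That stands for the detail, and the point asks for none of it. It does not rescue a stated diagnostic that cannot work, or a stated response that does not match it.

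A reader might infer more than the text supports:

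- **That the whole rule hangs on detection.** It does not, because missing outcomes of main interest trigger imputation on their own.
- **That the imputation excludes a missing-not-at-random component.** Bayesian structural equation modelling can carry a missingness model. The text neither includes nor rules one out, so the supportable statement is that none is stated.
- **That dropout bias in general is ignored.** The imputation and the mixed models of section {20a} both address missing-at-random loss. Section {18b} invites all students to assessments whatever their attendance. Only missing-not-at-random bias lacks a stated remedy.
- **That one completed dataset will be analysed as if fully observed, or that class is left out of the imputation.** The aim of obtaining complete outcome data fits multiple imputation equally well, and nothing is said about class either way. No claim about standard errors or type I error follows.
- **That the bias is a fixed share of a 6-point effect.** Section {14} presents 7% and 13% as between-group differences, not as arm rates, so their difference is not a planned effect between arms.

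The closing words of section {20b} sit under the item on subgroup and adjusted analyses. They do not clearly forbid a missing-data sensitivity analysis, but read literally they leave no room for one and should be aligned.

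**Conclusion.** The point holds in this limited form. The detection step in section {20c} cannot do what it says. It is redundant for the primary outcomes, and the response named for a declared missing-not-at-random pattern has no stated missing-not-at-random element. This is a fault in a stated rule as well as an omission.

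The size depends on values that cannot be observed. At the anticipated 20% loss, the illustrated shortfalls of 5 to 13 points among missing intervention students give an overstatement of 1.0 to 2.6 points, and a 7-point shortfall among missing control students alone gives an understatement of 1.4. These figures assume equal loss in both arms and imputation at the observed rate within arm, and they scale in proportion to the fraction missing. They show why a sensitivity analysis is needed; they do not predict the bias in this trial.

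**What to change.** 1. Delete the detection step from section {20c}. A descriptive comparison of students with and without outcome data may stay, provided that it is not said to identify the mechanism.
2. State that the primary analysis, whether the planned mixed model or the imputation, assumes missing at random.
3. Prespecify one missing-not-at-random sensitivity analysis. Delta-adjusted imputation would serve: vary the missing outcomes in each arm separately, in both directions, over a range fixed before outcome data are seen, and report where the conclusion changes, if it does.
4. Align the closing sentence of section {20b} so that this analysis is allowed.

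The cost is rewording two short sections and running one extra analysis. The sample size, data collection and visit schedule are unaffected.

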### Plans to give access to the full protocol, participant-level data, and statistical coding {31c}

The protocol has been registered at the ClinicalTrial.gov registry. The data will be shared only upon reasonable request to be evaluated by the PI.

## Oversight and monitoring

### Composition of the coordinating center and trial steering committee {5d}

The trial will be arranged and implemented under the responsibility of the IRCCS Istituto Centro San Giovanni di Dio Fatebenefratelli of Brescia. Three units of this Institute will carry out the study: the Unit of Psychiatry, the Unit of Biological Psychiatry, and the Service of Statistics. The coordinating center of the trial will be the Unit of Psychiatry. The PI will organize monthly meetings with the researchers’ staff to monitor the progress of the trial and to check if the plan is being followed. The PI will be responsible for preparation of the protocol, revisions, and periodic study reports. The PI will send annual reports about the study’s progress to the Ethics Committee. Moreover, two reports about project activity will be sent to the Ministry of Health at the midpoint and end of the project. The data management team will include the PI and the Service of Statistics. The data management team will assure quality data checks and maintenance of the database. Given the low risks added by the study, an independent oversight committee will not be established.

### Composition of the data monitoring committee, its role and reporting structure {21a}

Given the minimal risks of the present trial, a formal data monitoring committee will not be established. However, following local standards, data monitoring will be performed by an independent local ethics committee (Comitato Etico IRCCS San Giovanni di Dio, Fatebenefratelli, [name]) that will oversee the study’s progress through periodic reports.

### Adverse event reporting and harms {22}

Given the type of research, specific plans for severe adverse events (SAEs) have not been formulated since neither SAEs are anticipated. Based on a literature review, no study reported harm for students who participated.

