##### Impulsive behaviors

Checklist for Impulsive Behaviors (CIB)

This CIB is an ad hoc 15-item checklist created to determine the frequency of impulsive behaviors: alcohol use (4 items), substance use (2 items), internet addiction (4 items), gambling (1 item), non-suicidal self-injury (2 items), unprotected sex (1 item), and binge eating (1 item). Participants will be asked to indicate, on a 5-point Likert scale, the frequency of impulsive behaviors that occurred in the previous month (never; only once a week; two or three times a week; at least 4 times a week). Moreover, the checklist includes a section to evaluate the lifetime frequency of each behavior on a 6-point Likert sale (1–2 times, 3–5 times, 6–9 times, 10–19 times, 20–39 times, at least 40 times). For our primary outcome analysis, we will assess the difference between the two groups in the proportion of participants categorized as “improved” at post-intervention. Specifically, we will consider as “improved” those participants with a difference of at least one category toward improvement from baseline to post-intervention in the frequency of impulsive behaviors. Intervention efficacy will be established by treatment success, defined as at least 13% (i.e., 2/15 item) between groups after the intervention.

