### Plans to promote participants’ retention and complete follow-up {18b}

To promote both involvement in the evaluation and to ensure that each participant can complete the entire evaluation, all activities will be planned in agreement with school personnel during the school period. Moreover, one or two teachers will be identified as the contact persons for each class. We did not set criteria to define drop-out; however, we registered attendance at the sessions for each participant. All participants will be invited to complete and follow-up questionnaires independent of attendance.

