### Frequency and plans for auditing trial conduct {23}

The PI will organize monthly meetings with the researchers’ staff to monitor the progress of the trial and to check if the plan is being followed. The PI will send annual reports about the study’s progress to the Ethics Committee with the following information: the number of recruited participants, the number of participants who completed the study, the number of refusals, the number of drop-outs.

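### The named monitor's listed report carries no harm data, SAE plans are waived, and the primary CIB endpoint cannot separate worsening from no change, although self-injury and depression are collected

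*Protocol article*

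**What the plan says.** Five statements in the protocol article bear on this.

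- **Adverse event reporting and harms {22}:** "specific plans for severe adverse events (SAEs) have not been formulated since neither SAEs are anticipated". The second stated basis is a literature review in which "no study reported harm for students who participated". The section describes no collection of other adverse events.
- **Data monitoring committee {21a}:** "a formal data monitoring committee will not be established"; instead, "data monitoring will be performed by an independent local ethics committee", by way of periodic reports.
- **Coordinating center and steering committee {5d}:** "Given the low risks added by the study, an independent oversight committee will not be established".
- **Auditing trial conduct {23}:** the annual report to the ethics committee gives "the number of recruited participants, the number of participants who completed the study, the number of refusals, the number of drop-outs".
- **Retention and follow-up {18b}:** "We did not set criteria to define drop-out".

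Among the outcomes, the CIB is a primary measure whose content includes "non-suicidal self-injury (2 items), unprotected sex (1 item), and binge eating (1 item"). The PHQ-9 is a secondary outcome, with cutoffs that separate levels of depression severity.

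**The concern.** The article itself settles who monitors, what the monitor receives, and that there is no plan for severe events. So this is not a detail that a condensed article has left to a fuller document. Taken together, the statements name a monitor and list a report from which it could not see harm.

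The premise also sits badly with the trial's own content. The background links emotional dysregulation with self-harm and suicidal ideation, and the trial asks students about self-injury and depression. The literature basis is thin by the article's own account: the background says evidence on maladaptive behaviors is scant and that most existing studies have no follow-up assessment. An absence of reported harm in such a literature says little.

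Two things are at stake: whether the named monitor could notice a worsening during the trial, and how firmly the final report could speak about harm from a universal school programme.

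**Working it through.** The plan gives no figure for this point, so there is none to reproduce. The check sets the sections side by side.

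**1. What the monitor receives.** Section {23} lists four quantities: recruited, completed, refusals, drop-outs.
- Concerning harm: 0 of 4.
- Stated by arm: 0 of 4.
- Without a definition: 1 of 4 (drop-outs, by {18b}).

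**2. What the trial collects that bears on harm.**
- Self-injury: 2 of 15 CIB items, 2/15 = 13%. Follow-up of the CIB at all four assessments is supported by Trial design {8}, which assesses everyone at baseline, post-intervention, 3 and 6 months, and by Objectives {7}, which expects the primary changes to persist at 3 and 6 months.
- Depression: PHQ-9. The Secondary outcomes text fixes only baseline and post-intervention. The visit-by-instrument schedule is Table 1, which is not shown, so later PHQ-9 assessments can be neither confirmed nor excluded.

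**3. Whether another section closes the gap during the trial.**
- {11b}: no special criteria for discontinuing or modifying the intervention.
- {19}: the review after each assessment session is a data-quality check.
- {21b}: no interim look is described.
- {5d} and {23}: monthly staff meetings follow progress and adherence to plan. The two reports to the Ministry of Health concern project activity, and the Ministry is not the named monitor.

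None is described as carrying self-injury or depression data to the ethics committee.

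**4. What the final analysis could show.** The primary CIB endpoint is the proportion improved. In an arm of N students let I be improved, U unchanged and W worse, so that N = I + U + W. The endpoint is I/N. For fixed I, any split of N − I between U and W gives the same value, so the endpoint carries no information on W.

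The Statistical methods {20a} also plan generalized mixed models of dysfunctional behaviors by group and time, which can show average worsening. How the 15 items enter is not stated. If they are weighted equally (an assumption), a one-category rise on both self-injury items adds 2/15 = 0.13 of a category to the item mean, and a one-category fall on any two of the other 13 items cancels it. Self-injury could thus rise with no change in the overall score. PHQ-9 mean change is a separate planned outcome and does not suffer this dilution.

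**The case against.** The strongest reply is that the sections are compatible. Section {21a} describes the committee's task as following study progress, {23} lists progress counts, and no text assigns it harm monitoring. The intervention is 8 hours of school psychoeducation, and low risk is given as the reason for having no formal committee. Measuring self-injury as an efficacy outcome does not mean that the trial expects to cause it. All this stands as a defence of having no formal committee. It does not explain why a body named for data monitoring has no harm item in its listed report when the data exist.

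A reader might infer several stronger things that the article does not support.

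- **That harm in one arm would go unseen, or that nothing could be said about safety.** The mixed models and PHQ-9 means could show average worsening. The supported claim is that it would not reach the monitor during the trial and that self-injury could be diluted at the end.
- **That every assessment covers both self-injury and depression.** For the PHQ-9 this cannot be verified without Table 1.
- **That all participants are minors.** Eligibility is 16–19 years.
- **That the harm can be counted.** With about 225 students per arm (450/2) and an assumed past-month self-injury prevalence of 5–15%, 11 to 34 students per arm would report it (0.05 × 225; 0.15 × 225). That is assumed background prevalence; it would be the same if the intervention were harmless.

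Two practical objections stand and shape the fix. Data analysts are blinded under {17a} and {17b}, so open by-arm tables from the Service of Statistics would conflict with blinding. And an annual report may arrive after a given class has finished its four monthly sessions, so any benefit during the trial is mainly for later classes.

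**Conclusion.** The point holds in a limited form. The listed report to the named monitor contains 0 harm items out of 4, plans for severe events are waived as not anticipated, and no other described route takes worsening to the monitor while the trial runs. In the final analysis the primary CIB endpoint is blind to worsening, and self-injury is 2 of 15 items in the broader comparison, so an increase could be diluted even though average worsening could be detected.

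The undefined drop-out count is a smaller, adjoining fault: it does not affect harm detection, but it leaves one of the four reported numbers without a stated meaning.

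The conclusion assumes that the report contains what {23} lists and no more. The dilution argument further assumes equal item weights. No excess of harm is estimated, because the article offers no basis for one.

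**What to change.** 1. **Final analysis.** Report as a harm outcome, by arm and at each time point where the instrument is given, the number and proportion of students with any past-month self-injury on the CIB, with an increase in self-injury from baseline, and with a worse PHQ-9 severity category than at baseline.
2. **Annual ethics committee report.** Add a harm summary from the same data, either pooled or with coded arms, so that the analysts stay blinded.
3. **Drop-outs.** Replace this count in {23} with the number not completing each assessment.
4. **Text.** Reconcile {21a}, {22} and {23} with the CIB and PHQ-9 outcome sections, so that the monitoring role, the report content and the adverse-event statement agree with what is collected. How individual disclosures are handled is for the investigators and the ethics committee to set.

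The cost is one extra table per report from questionnaires already collected and entered, the care needed to keep arms coded, and a few lines of wording. No new procedure for students is involved.
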